#### Patient-level randomization

Patient will be individually randomized in a 1:1 ratio to iCanDecide-S vs. iCanDecide-ESE using a dynamic allocation algorithm based on methods by Pocock and Simon [30]. The goal of the algorithm is to maintain arm balance with respect to the following stratification factors which are prognostic factors on study outcomes, especially knowledge: race (non-Hispanic White; non-Hispanic African American; Other—including Hispanic) and education status (≤ high school; some college; college graduate or more). Patients are assigned to the arm that leads to more imbalance 10% of the time to ensure some randomness in the algorithm.

### Concealment mechanism {16b}

The patients are allocated to one of the two iCanDecide versions but which version of the intervention they receive is concealed to them. Clinics and clinicians are not aware to which version their patients are randomized. The clinics/clinicians are made aware of their assignment 2 weeks prior to their Clinician Dashboard step.

### Implementation {16c}

Following enrollment, patients will be randomized by the Alliance Statistics and Data Management Center (SDC) as described above. Their allocation assignment will be securely sent to the UM CHCR technology development team. The CHCR team will send the patient an email with a direct link to her assigned group. All twenty-five clinics will be randomized at study initiation into one of seven steps (including one that never utilizes the Clinician Dashboard, one that always uses the Clinician Dashboard and five that begin to use the Clinician Dashboard at different times).

## Assignment of intervention: blinding

### Who will be blinded {17a}

The Alliance SDC and CHCR technology team cannot be blinded to the trial arm to which patients are assigned, or to which clinics are randomized, as they are responsible for randomization and allocation. The study investigators (principal investigators and co-investigators) are blinded to the trial arm. Patients will be blinded to which of the iCanDecide websites is the intervention being tested (iCanDecide-ESE) and which is the control (iCanDecide-S). Clinics cannot be blinded because they will be aware roughly 2 weeks prior to when they are allocated to start the Clinician Dashboard to receive training.

### Procedure for unblinding if needed {17b}

There is no requirement for this.

## Data collection

### Plans for assessment and collection of outcomes {18a}

Data collection for the primary, secondary, and additional outcomes related to locoregional treatment decision making and communication will be done via patient survey at 5 weeks post-surgery (first follow-up assessment). This will be done via the Patient Cloud (“ePRO”) application that will be added to the participant’s smart device (iPhone or Android) at time of enrollment, with a paper survey as a backup option for those who desire it. Participants will be surveyed again 9 months after registration (second follow-up assessment) to assess measures related to systemic treatment decision-making and communication (via ePRO or paper option). At 9 months after registration, participant’s medical records will be reviewed by the CRA for treatment information (surgery performed, use of radiation therapy, chemotherapy treatment). Clinicians will complete the same survey three times throughout the study, at time of registration, and 9 and 18 months after registration.

### Plans to promote participant retention and complete follow-up {18b}

Patients will be reminded by the CRA/clinical staff to log in and complete assessments. Clinicians will be reminded by the CRA/clinical staff to complete their assessments. Patients and clinicians receive incentives following completion of assessments.

### Data management {19}

Data will be managed by the SDMC.

### Confidentiality {27}

Data are stored in secure and confidential software systems affiliated with the Alliance and NCORP.

### Plans for collection, laboratory evaluation, and storage of biological specimens for genetic or molecular analysis {33}

Not applicable for this study.

## Analysis

### Statistical methods for primary and secondary outcomes {20a}

We will follow an intention to treat approach [31], using all available data, regardless of group assignment or whether patients viewed the patient-facing decision tool. The data as collected will have a nested structure: patients nested within clinicians, within clinics and regions of the country. Descriptive analyses will summarize patient, clinician, and clinic characteristics.

#### Primary outcome analysis

As described, we are testing two interventions, one randomized at the individual level (𝑖) and one at the clinic level (𝑗), rolled out to clinics over six trial time periods (𝑘). The interventions are fully crossed (with intervention and control patients within both intervention and control clinics for every time period). The linear mixed model for the continuous primary outcome (𝑦) patient knowledge has been adapted to a factorial design by adding an individual-level intervention to the model for a hybrid stepped wedge design [32]: 𝑦_𝑖𝑗𝑘_ = 𝛽_0_ + 𝜃_1_𝑥_1𝑖𝑗𝑘_ + 𝜃_2_𝑥_2𝑗𝑘_ + 𝛽_𝑘_𝑡_𝑘_ + 𝑢_𝑗_ + 𝑒_𝑖𝑗𝑘_. Here, 𝑦_𝑖𝑗𝑘_ denotes the response corresponding to individual 𝑖 at time period 𝑘 from clinic 𝑗 (𝑖 = 1, … , 𝑚_𝑗𝑘_ ; 𝑗 = 1, … , 25; 𝑘 = 1, … , 6). The variable 𝑥_1𝑖𝑗𝑘_ (=0, 1) denotes the intervention status of patient 𝑖 enrolled in clinic 𝑗 at time period 𝑘. The variable 𝑥_2𝑗𝑘_ (=0, 1) denotes the intervention status of this patient’s clinic 𝑗 at the 𝑘𝑡ℎ time period. The variable 𝑡_𝑘_ (=0, 1) is the indicator for time period 𝑘 and the term 𝛽_𝑘_ represents the corresponding fixed categorical effect to model the underlying secular trend (𝑘 in 1, …, 5, 𝛽_6_ = 0 for identifiability). The random effect 𝑢_𝑗_ is a random intercept for clinic 𝑗 and represents the time invariant deviation of the 𝑗𝑡ℎ clinic from the population average. The term 𝑒_𝑖𝑗𝑘_ is the patient error term. The term 𝛽_0_ is the intercept. The terms 𝜃_1_ and 𝜃_2_ represent the intervention effect of iCanDecide-ESE and the intervention effect of the Clinician Dashboard, respectively. As one of the most effective ways to improve the statistical power in cluster randomized trials [32, 33], the two patient-level stratification factors (race; education status) as well as an indicator for Hispanic/Latina (yes; no) that are expected to be strongly associated with the outcome knowledge will be included in the model as supportive analysis. The model assumes that an underlying time effect is the same for each clinic. To allow for potential clinic-level fluctuations of the time effect related to the roll out of the Clinician Dashboard, the random effect (𝑢𝑡)_𝑘_ (i.e., a clinic effect interacting with time) will be included in sensitivity analysis. Additionally, sensitivity analyses will account for nesting within clinician.

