### Sample size {14}

Sample size depends on the near minimax stepped wedge/parallel hybrid design as described by Girling and Hemming [28]. This design provides close to the maximal possible efficiency across a range of intra-cluster correlations (ICCs) from 0 to 0.2, where larger ICCs are expected for our primary outcome of knowledge as seen from the prior iCanDecide randomized clinical trial (RCT) [3]. Specifically, in our previous iCanDecide trial, we calculated an ICC of 0.15 and a moderate effect size for the iCanDecide decision tool of 0.5 standard deviations. This effect size is equivalent to a little less than one additional question being answered correctly by those who received the intervention.

For SharES, we calculated the sample size required to detect a somewhat smaller standardized effect size of 0.35, which results in only two out of three women getting an additional question correct. Thus, for the planned hybrid stepped wedge design testing the clinic level intervention, we will recruit 25 clinics with a target total sample size of 600 evaluable patients (approximately four patients per clinic per time period) [28–31]. We estimate about 15% will not complete the first follow-up assessment (5 weeks post-surgery), based on our prior iCanDecide trial [3], so we plan to enroll at least 700 participants or around 5 patients per clinic per period. This will allow us to have at least 80% power (alpha=0.05) to detect differences of 0.35 standard deviations between intervention and control subjects for the clinic level intervention (Clinician Dashboard vs. none) and 0.25 standard deviations for the individual-level intervention (ICanDecide-ESE vs. ICanDecide-S) across a wide range of ICCs (0.01 to 0.20). The interaction effect between the two interventions would have to be at least 0.5 standard deviations, or about one additional question correct for each subject, comparable to our effect size in our current intervention, for us to be able to detect it at conventional significance levels.

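### The primary model leaves out the race and education factors that balance the patient randomisation, so the iCanDecide-ESE test is mildly conservative and both co-primary tests give up some power

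*Protocol article*

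**What the plan says.** Protocol article, *Patient-level randomization*: patients are randomised 1:1 "using a dynamic allocation algorithm based on methods by Pocock and Simon". The factors are race (three levels) and education (three levels), and the aim is to "maintain arm balance with respect to the following stratification factors which are prognostic factors on study outcomes, especially knowledge". The algorithm keeps a random element: "Patients are assigned to the arm that leads to more imbalance 10% of the time to ensure some randomness in the algorithm".

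Protocol article, *Primary outcome analysis*: the linear mixed model for knowledge "has been adapted to a factorial design by adding an individual-level intervention to the model for a hybrid stepped wedge design". As written out, it has an intercept, the ESE effect θ₁, the Dashboard effect θ₂, fixed period effects, a random clinic intercept and patient error. It has no race or education term. The text then turns to the two stratification factors and a Hispanic/Latina indicator. It introduces them with "As one of the most effective ways to improve the statistical power in cluster randomized trials" and says of them "that are expected to be strongly associated with the outcome knowledge will be included in the model as supportive analysis".

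The two co-primary sections take their tests from θ₁ and θ₂ of that single model. ESE is tested first at 0.05, the Dashboard is tested only if ESE succeeds, and the key secondary family is tested only if both succeed.

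**The concern.** The protocol's reason for using the covariates is power, but a supportive analysis gives no power to the tests that decide the trial. The protocol has therefore fixed a choice that defeats its own argument. This is not a detail left to a later document.

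There is also a mismatch between design and analysis. Dynamic allocation removes most of the chance difference between arms in race and education, so the ESE estimate varies less from trial to trial than it would under simple randomisation. A model without those factors still counts their contribution in the residual variance. Its standard error for θ₁ is then too large, and the test rejects less often than 5% under the null.

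The ESE test is the first gate, so any power it loses carries to the Dashboard and to the key secondary outcomes.

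**Working it through.** **Inputs from the protocol.** 600 evaluable patients; 25 clinics; 6 periods; about 4 patients per clinic-period; 5 clinics always on the Dashboard, 5 never, 3 at each of 5 steps; ICC 0.15 from the prior trial, range 0.01 to 0.20; target effects 0.25 SD (ESE) and 0.35 SD (Dashboard); α = 0.05.

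**Assumed.** α is two-sided. R², the share of within-clinic variance in knowledge explained by race and education, is 0.05, 0.10 or 0.20; the protocol gives no value. The within-clinic share is the relevant one, because the clinic intercept already absorbs much of the between-clinic part.

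**1. The stated power, without covariates.**
- ESE: SE = √(4(1 − ICC)/600). At ICC 0.15 this is √(3.4/600) = 0.0753. Power at 0.25 SD is Φ(0.25/0.0753 − 1.96) = 91.3%. At ICC 0.01 it is 86.8%, and at 0.20 it is 92.8%.
- Dashboard: generalised least squares variance for the stated layout gives SE 0.1189 at ICC 0.15. Power at 0.35 SD is Φ(0.35/0.1189 − 1.96) = 83.7%. At ICC 0.01 it is 95.7%, and at 0.20 it is 83.5%.

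The claim of "at least 80% power (alpha=0.05) to detect differences of 0.35 standard deviations between intervention and control subjects for the clinic level intervention" is therefore reproduced, as is the 0.25 SD claim for ESE.

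**2. True size of the unadjusted ESE test.** If the arms are balanced on the factors, the true SE of θ₁ is √(1 − R²) times the SE the model reports, so size = 2Φ(−1.96/√(1 − R²)). This was checked by simulating Pocock-Simon allocation with the 90/10 coin: 4,000 null runs, ICC 0.15 treated as known, assumed race and education mixes, no attrition. Monte Carlo error is about √(0.05 × 0.95/4000) = 0.003.

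| R² | Formula, unadjusted | Simulated, unadjusted | Simulated, adjusted |
|---|---|---|---|
| 0.05 | 0.044 | 0.044 | 0.049 |
| 0.10 | 0.039 | 0.037 | 0.047 |
| 0.20 | 0.028 | 0.033 | 0.053 |

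Under simple randomisation at R² = 0.10 the unadjusted size was 0.051, so the balancing causes the conservatism. The simulated size of the unadjusted Dashboard test was 0.044 to 0.051, which is nominal.

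**3. Power at ICC 0.15.** For ESE with balanced arms, unadjusted power is Φ((0.25/SE − 1.96)/√(1 − R²)) and adjusted power is Φ(0.25/(SE√(1 − R²)) − 1.96). For the Dashboard, the residual variance (1 − ICC) is multiplied by (1 − R²) and the clinic variance is left unchanged.

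| R² | ESE unadjusted | ESE adjusted | Gain (points) | Dashboard unadjusted | Dashboard adjusted |
|---|---|---|---|---|---|
| 0.05 | 91.9% | 92.6% | 0.7 | 83.7% | 85.2% |
| 0.10 | 92.4% | 93.8% | 1.4 | 83.7% | 86.6% |
| 0.20 | 93.6% | 96.0% | 2.4 | 83.7% | 89.6% |

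**4. The ESE gain as sample size, judged at 80% power.** The unadjusted detectable difference is (1.96 + 0.8416√(1 − R²)) × SE. The adjusted one is 2.8016√(1 − R²) × SE. At R² = 0.10 these are 2.758 × 0.0753 = 0.208 and 2.658 × 0.0753 = 0.200 SD. The squared ratio gives the equivalent gain in patients: about 4%, 8% and 17% at R² 0.05, 0.10 and 0.20.

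**The case against.** The strongest reply is that little is at stake. Both tests meet the promised 80% power without any covariate, no false claim becomes more likely, and the adjusted model is already prespecified with named covariates. On this view the dispute is only about which of two planned models is called primary. Most of that stands and it limits the weight of the point. It does not remove it, because the model called primary decides whether the testing sequence proceeds.

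The size of the conservatism can also be questioned. Allocation is not balanced within clinic, 10% of assignments go the other way, and the protocol expects about 15% of patients to miss the first follow-up, which restores some imbalance. If that loss is random and restores 15% of the covariate variance, √(1 − R²) becomes √(1 − 0.85R²), and size is about 4.5%, 4.0% and 3.1%. The effect is smaller but in the same direction.

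Three stronger readings are tempting, and the protocol does not support them:

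- **Adjustment is worth 1/(1 − R²) − 1, or 5%, 11% and 25% more patients, for ESE.** This assumes that the unadjusted estimate still carries the covariate variance, which contradicts the premise that allocation has removed it. The figures in step 4 are the consistent ones.
- **The Dashboard estimate is biased because clinic randomisation is unstratified.** Chance differences in patient mix under randomisation cost precision and do not bias the estimate. The clinic intercept and the 15 of 25 clinics that change status absorb part of them, and the test keeps nominal size.
- **No patient can be lost under any of the proposed covariates.** This follows for race and education, which are needed to allocate each patient. It does not follow for the Hispanic/Latina indicator, which is not a separate allocation factor.

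**Conclusion.** The concern holds as a matter of efficiency and of a standard error that does not match the design. The protocol balances on two factors it calls prognostic and gives power as the reason for modelling them, then keeps them out of the confirmatory model.

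The direction is certain if the factors predict knowledge at all. The size rests on R², which is assumed, and on a two-sided α. Over R² 0.05 to 0.20 at ICC 0.15, the loss is about 1 to 2 points of power for ESE and about 1 to 6 points for the Dashboard. If the two tests are treated as independent, the chance of passing both gates at R² = 0.10 is 0.924 × 0.837 = 77% unadjusted and 0.938 × 0.866 = 81% adjusted.

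A reader might infer that the trial is underpowered or its error rate inflated; neither is so. The change is worth making because it costs almost nothing.

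**What to change.** In *Primary outcome analysis*, add race (three levels) and education (three levels) as fixed effects to the primary model for knowledge. Do the same in the models for cancer worry and self-efficacy. Report the model without them as the supportive analysis. Make the change before any outcome comparison is seen, so that the choice between the two models is not open later.

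The Hispanic/Latina indicator can be added as the protocol already intends. Any missing values would be handled by the multiple imputation that the protocol's missing-data section provides for predictor variables.

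Cost: one sentence, four degrees of freedom for race and education (five with the indicator), and no new data. Because allocation requires race and education, adjusting for them loses no patient.

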#### Co-primary objective #1

The analysis effectively reduces to a typical multisite, patient-level RCT of iCanDecide-S vs. ESE [32]. We will compare the interventions on patient knowledge, obtained at the first follow-up (5 weeks) assessment post-surgery. The effect of the patient-level intervention will be quantified by the coefficient 𝜃_1._

#### Co-primary objective #2

The primary estimate of the effect of the Clinician Dashboard cluster-level intervention on the primary outcome knowledge obtained at the first follow-up (5 weeks) assessment is quantified by the coefficient 𝜃_2_ .

Although a single model is estimated to address the two co-primary objectives, a fixed-sequence testing strategy will be applied to control the Type I error rate at 0.05 across the two corresponding primary comparisons. The iCanDecide-ESE vs iCanDecide-S comparison will be tested first at the significance level *α* = 0.05. Provided that the result achieves statistical significance at the 0.05 level, the Clinician Dashboard vs no Dashboard will be tested at the 5% significance level.

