#### Secondary outcome analysis

We believe the two key secondary outcomes (cancer worry, breast cancer self-efficacy) will provide supportive information about the effectiveness of the iCanDecide-ESE and Clinician Dashboard on the primary outcome of knowledge. A gatekeeping statistical strategy will be used to control the type I error rate at 0.05 across the primary and this key secondary family of outcomes such that when both effects on the primary outcome of knowledge are demonstrated, this family of key secondary outcomes will be examined and may contribute important supportive information about the effectiveness of the interventions. The secondary family of tests comprises four tests (two for each secondary outcome) that will be conducted and will be tested with the Holm procedure [29]. The linear mixed model described will be separately fit for each continuous outcome (cancer worry; self-efficacy). The self-efficacy (or cancer worry) effect of the individual-level intervention will be quantified by the coefficient 𝜃_1_. The estimate of the effect of the Clinician Dashboard cluster-level intervention on self-efficacy (or cancer worry) will be quantified by the coefficient 𝜃_2_.

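### The 80% power stated for the Clinician Dashboard is for a stand-alone test; under the fixed sequence the chance of a confirmatory Dashboard result is about 76% to 83%

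*Protocol article*

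**What the plan says.** All references are to the protocol article.

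- **Objectives {7}** names two primary co-objectives, one for iCanDecide-ESE and one for the Clinician Dashboard, both on knowledge.
- **Sample size {14}** plans "25 clinics with a target total sample size of 600 evaluable patients (approximately four patients per clinic per time period"). It then states: "This will allow us to have at least 80% power (alpha=0.05) to detect differences of 0.35 standard deviations between intervention and control subjects" for the Dashboard, and "0.25 standard deviations for the individual-level intervention (ICanDecide-ESE vs. ICanDecide-S) across a wide range of ICCs (0.01 to 0.20") for ESE. From the prior trial, "we calculated an ICC of 0.15". The section does not mention the order of testing.
- **Co-primary objective #2** sets a fixed sequence. ESE is tested first at 0.05. Then: "Provided that the result achieves statistical significance at the 0.05 level, the Clinician Dashboard vs no Dashboard will be tested", also at 5%.
- **Secondary outcome analysis** adds a further condition: "when both effects on the primary outcome of knowledge are demonstrated, this family of key secondary outcomes will be examined".

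**The concern.** Under a fixed sequence, the second hypothesis can be claimed only if both tests succeed. A power figure for the second test that leaves out the first is the chance of success given that the first test has been passed. It is not the chance that the trial will support the claim. The sample size section gives both co-primary comparisons the same assurance, although the Dashboard comes second.

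A reader planning around the 80% would therefore overestimate the chance of a confirmatory Dashboard result. The gap depends on the true ESE effect on knowledge. The ESE comparator is the standard tool, which the intervention description calls proven for knowledge, and ESE adds emotional-support modules to the same content. A gain below 0.25 SD is therefore worth considering when planning.

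**Working it through.** **Inputs.** 25 clinics, 6 periods, 4 evaluable patients per clinic-period (600), effects of 0.35 SD (Dashboard) and 0.25 SD (ESE), and ICC 0.01 to 0.20 come from the trial design and sample size sections. The clinic-level randomization section gives 5 clinics always on, 5 never on and 3 starting at each of T2 to T6. Patients are allocated 1:1. Two-sided tests, total SD 1 and a normal approximation are my assumptions.

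**Step 1: Dashboard standard error** under the stated model (fixed period effects, random clinic intercept). With σ² = (1−ICC)/4 and τ² = ICC,

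Var(θ₂) = Iσ²(σ² + Tτ²) / [(IU−W)σ² + (U² + ITU − TW − IV)τ²]

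- I = 25 clinics, T = 6 periods, and U = 75 clinic-periods with the Dashboard on.
- W is the sum of squared period totals: 5² + 8² + 11² + 14² + 17² + 20² = 1095.
- V is the sum of squared clinic totals: 5×36 + 3×(25+16+9+4+1) = 345.
- So IU−W = 780, and U² + ITU − TW − IV = 5625 + 11250 − 6570 − 8625 = 1680.

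At ICC 0.15, σ² = 0.2125 and Var = 25×0.2125×1.1125 / (780×0.2125 + 1680×0.15) = 5.910/417.75 = 0.01415, so SE = 0.1189. Power = Φ(0.35/0.1189 − 1.96) = Φ(0.98) = 83.7%.

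**Step 2: ESE standard error.** The contrast is essentially within clinic, so SE = √(4(1−ICC)/600). At ICC 0.15 this is √(3.4/600) = 0.0753. Power = Φ(0.25/0.0753 − 1.96) = Φ(1.36) = 91.3%.

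**Step 3: apply the sequence.** In the crossed design the two estimates are nearly uncorrelated, so P(Dashboard claimed) ≈ P(ESE significant) × P(Dashboard significant). At ICC 0.15 this is 0.913 × 0.837 = 0.764.

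| ICC | ESE alone | Dashboard alone | Dashboard through the sequence |
|---|---|---|---|
| 0.01 | 86.8% | 95.7% | 83.1% |
| 0.05 | 88.1% | 89.5% | 78.9% |
| 0.10 | 89.8% | 85.3% | 76.6% |
| 0.15 | 91.3% | 83.7% | 76.4% |
| 0.20 | 92.8% | 83.5% | 77.5% |

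The two middle columns reproduce the article's claim of at least 80%. The last column meets it only at ICC 0.01. Simulating the planned model (3,000 runs per ICC) gave 83.2%, 78.5%, 75.4% and 75.7% at ICC 0.01, 0.05, 0.15 and 0.20.

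**Step 4: smaller ESE effects**, at ICC 0.15 with the Dashboard at 0.35 SD.

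| True ESE effect | ESE power | Dashboard through the sequence |
|---|---|---|
| 0.20 SD | 75.7% | 63% |
| 0.15 SD | 51.3% | 43% |
| 0.10 SD | 26.4% | 22% |
| 0 | 5.0% | 4% |

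**Step 5: other evaluable numbers the article supports.**

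- 700 enrolled with 15% loss gives 595 evaluable, and 76.0% at ICC 0.15.
- Five enrolled per clinic-period is 5×25×6 = 750. With 15% loss that is about 638 evaluable, and 85.6%, 81.7%, 79.4%, 79.3% and 80.3% across the five ICCs.
- 700 enrolled at the 92% completion cited in the missing-data section gives 644 evaluable, and 79.8% at ICC 0.15.

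**Step 6: Holm over the two primary tests, for comparison.** Dashboard power = P(p₂<0.025) + P(0.025≤p₂<0.05) × P(p₁<0.025). At ICC 0.15 this is 0.758 + 0.079×0.860 = 82.6%. The ESE figure is 0.860 + 0.053×0.758 = 90.0%. Over the five ICCs at the planned effects, Dashboard power is 82.6% to 95.0% and ESE power is at least 86.3%. If ESE has no effect, Dashboard power under Holm is 92.5% at ICC 0.01, 76.0% at 0.15 and 75.8% at 0.20.

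**The case against.** The strongest reply is that nothing has been miscalculated. The section gives power for each comparison at alpha 0.05, the Dashboard is tested at that same level once reached, and the stand-alone figures hold at every ICC in the range. Marginal power is often quoted under a fixed sequence. The article also points to a fuller protocol, not shown here, which may qualify the figure. All of this stands as a description of the calculation. It does not tell the reader of this section that the 80% excludes a condition imposed by the article's own testing rule.

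The size also needs care. At the planned effects the gap is a few points, and with about 640 evaluable patients it nearly closes. The larger losses assume an ESE effect below the planned one, which is the known price of a fixed sequence.

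A reader might infer more than the document supports:

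- *That the sequence is invalid.* It controls the type I error rate at 0.05. Putting the patient tool first is defensible, because both interventions belong to one system and the Dashboard is populated by patients' use of the tool.
- *That the Dashboard may go unevaluated.* θ₂ comes from the same single model whatever ESE shows. Only the formal claim is lost.
- *That Dashboard power is only 0.80 × 0.80 = 64%.* Both tests exceed the stated floor in this design, so the product is 76% to 83%.
- *That Holm, or separate gates for each intervention's key secondary outcomes, is required.* These are alternative valid strategies. The article presents the key secondary outcomes as supportive, which is consistent with opening them only after both primary successes.

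**Conclusion.** The point holds as a mismatch between the sample size section and the testing rule. Under the fixed sequence, with 600 evaluable patients and both planned effects true, power for a confirmatory Dashboard finding falls 1 to 4 points short of 80% at every ICC evaluated from 0.05 to 0.20, and stays above 80% at 0.01. Because the key secondary family opens only when both primary tests succeed, the same joint probability is the chance of reaching it.

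The result rests on two-sided tests, the stated model with a constant clinic effect over time, equal cell sizes, a normal approximation with 25 clinics, and near-independence of the two estimates. The simulation supports the product to within about 2 points. This is a correction to a stated planning figure. It does not undermine the validity of the trial.

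**What to change.** In Sample size {14}, add that the 80% for the Dashboard is the marginal power of a 5% test and applies only once the ESE test has been passed. State that under the fixed sequence Dashboard power is about 76% to 83% over ICC 0.01 to 0.20, given a true ESE effect of 0.25 SD and 600 evaluable patients. Note how it falls for smaller ESE effects, and that the same figure is the chance of opening the key secondary family. This costs a few sentences and changes neither the design nor the analysis.

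As an option and not a correction, the sponsor could consider Holm across the two primary comparisons before unblinding. It would restore at least 80% for both at the planned effects, for about 0.5 to 1.3 points of ESE power. It would not remove the dependence on ESE: with no ESE effect, Dashboard power would still be about 76% at ICC 0.15 to 0.20. It would also slightly lower the chance that both primary tests succeed (76.0% against 76.4% at ICC 0.15), and so the chance of reaching the key secondary family under the current rule.
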